## **4. STATISCAL ANALYSIS PLAN**

### **4.1 Randomization and blinding**

The method used for randomization will be the stratified permuted block randomization. A total of ~208 patients will be randomized using both stratification and permuted blocks with random block sizes. Randomization will be stratified at each site (Granada and Pamplona) based on sex (men-women); with a total of two strata for each site. For this randomization scheme, a randomization list will be generated prior to the start of the trial; one randomization list being generated for each site and strata. A sequence of block sizes will be randomly generated where allowable block sizes will be 4 and 8. Within each block, each quarter of assignments will be randomly selected to be to one of the four possible groups (UC, early TRE, late TRE or self-selected TRE) using a parallel design (1:1:1:1 allocation ratio). As each participant is randomized into the trial, the participant will receive the next sequential assignment on the randomization list specific to his/her site and strata. The use of a random block size ensures that the next randomization assignment cannot be guessed. Because this will be a multicenter trial with two sites (Granada and Pamplona), randomization within each site will ensure that a site discontinuing participation in the trial or enrolling poorly would not affect the overall balance of the treatment groups. Stratifying by sex ensures that intervention groups are balanced on this important characteristic.

Personnel in charge of the evaluations of the primary outcome (VAT) and other ectopic MRI derived fat depots, fasting blood samples and statistical analysis will be blinded to the group assignment, whereas personnel in charge of the other measures as well as the intervention will be not blinded to the group assignment (open label).

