## **2. AIMS**

The overall aim of the present study is to investigate the efficacy and feasibility of three different 8h TRE schedules (i.e., early, late, and self-selected) compared to each other and to a usual-care (UC) intervention over 12 weeks on VAT, body composition and cardiometabolic health in adults with overweight/obesity.

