### 3.4 Lead-in period

There will be a 2-week lead-in period (before baseline measurements and group allocation; **Figure 1**) in which potential participants will continue with their habitual nutritional and physical activity habits. Potential participants will record daily their eating time and sleep and any adverse events using a mobile phone app (EXTREME: com.nnbi.app\_extreme, NNBi2020 S.L., Navarra, Spain). This data will be used to confirm that their eating window is  $\geq 12$  hours (see inclusion criteria, **Table 1**).

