### 3.5 Measurements

All measurements will be conducted both at baseline and 12 weeks post-intervention ( $\pm 3$  days) by experienced and trained personnel. Standardization of dietary intake, hydration, and physical activity will be implemented prior to the measurements of ectopic fat depots, body composition, and cardiometabolic risk factors. Specifically, participants will be instructed to observe a fasting period of 10 to 12 hours before their appointment, during which they will be advised to consume only water and abstain from solid food or other beverages.

It will be emphasized that they should have a complete meal at least 10 hours before the test. Furthermore, participants will be advised not to consume alcohol, drugs or diuretics within 24 hours before the test, and to avoid stimulants like caffeine or theine for 12 hours prior to the test. Lastly, participants will be instructed to refrain from engaging in moderate exercise or physical activity for 24 hours, and from vigorous exercise for 48 hours, prior to the test. For a comprehensive summary of the study's outcomes, refer to Table 2.

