### **3.7 Secondary outcomes**

#### **Body weight, anthropometry, and body composition**

Body weight and height will be measured using a stadiometer and scale (Seca model 799, Electronic Column Scale, Hamburg, Germany in both Granada and Pamplona) without shoes and with light clothing. Neck, waist, and hip circumferences will be measured following the ISAK procedures [20]. Bone mineral density, fat mass, and fat-free mass will be assessed using a dual-energy X-ray absorptiometry scan (QDR Discovery Wi Hologic, Inc., Bedford, MA, USA in Granada and Horizon Wi Hologic, Inc., Bedford, MA, USA in Pamplona).

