## **Quality of life**

Quality of life will be evaluated using the EuroQol 5 dimensions 5 levels (EQ-5D-5L), Rand Short Form 36 (SF-36), an adverse events questionnaire and menstrual questionnaire.

| Outcomes                                 | Baseline | 12-week post intervention |  |
|------------------------------------------|----------|---------------------------|--|
| Primary outcome                   |          |                           |  |
| Visceral adipose tissue (i.e., MRI)      | ✓        | ✓                         |  |
| Secondary outcomes                |          |                           |  |
| Body weight and anthropometry            | ✓        | ✓                         |  |
| Body composition (i.e., DXA)             | ✓        | ✓                         |  |
| Ectopic fat depots (i.e., MRI)           | ✓        | ✓                         |  |
| Cardiometabolic risk factors             | ✓        | ✓                         |  |
| Interstitial glycemic traits (i.e., CGM) | ✓        | ✓ *                       |  |
| Gut microbiota                           | ✓        | ✓ *                       |  |
| Sleep and physical activity (i.e., ACC)  | ✓        | ✓ *                       |  |
| Psychosocial assessment                  | ✓        | ✓                         |  |
| Eating behaviour assessment              | ✓        | ✓                         |  |
| Dietary habits                           | ✓        | ✓                         |  |
| Quality of life                          | ✓        | ✓                         |  |

sment will be conducted during the last two weeks of the intervention. Abbreviations: MRI, magnetic resonance imaging; DXA, dual-energy X-ray absorptiometry; CGM, continuous-glucose monitoring; ACC, accelerometry.

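### Section 4.1 leaves assessors of all non-MRI, non-blood measures unblinded without a reason, creating a week-12 observer-bias risk in secondary outcomes, chiefly tape-measured circumferences

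*Combined protocol and SAP*

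**What the plan says.** Section 4.1 (Randomization and blinding) divides the staff in two. Those who evaluate VAT, "other ectopic MRI derived fat depots, fasting blood samples and statistical analysis will be blinded to the group assignment". For everyone else, "personnel in charge of the other measures as well as the intervention will be not blinded to the group assignment (open label".

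The outcome descriptions in 3.7 show what falls in the second group. "Neck, waist, and hip circumferences will be measured following the ISAK procedures". "Bone mineral density, fat mass, and fat-free mass will be assessed using a dual-energy X-ray absorptiometry scan". Weight is taken on an electronic column scale and blood pressure with an automatic monitor. The outcome table in 3.7 lists anthropometry and "Body composition (i.e., DXA") as secondary outcomes, and the aim in section 2 is to study effects "on VAT, body composition and cardiometabolic health in adults with overweight/obesity".

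On timing, 3.5 says "All measurements will be conducted both at baseline and 12 weeks post-intervention", within 3 days. Section 3.4 places the lead-in "before baseline measurements and group allocation", which suggests that baseline is measured before allocation is known.

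The stated safeguards are trained personnel and standardised pre-test conditions (3.5), the ISAK procedure for circumferences (3.7), and coded data with blinded data handling and analysis (5.3). No duplicate or independent blinded measurement is described.

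**The concern.** Participants in an eating-window trial cannot be blinded. The person holding the tape or running the DXA scan can be, because neither task requires knowing the arm. A tape reading depends on where the tape is placed and how tightly it is held. An assessor who knows that a participant followed TRE and expects a smaller waist can shift the reading without intending to.

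Such a shift differs by group and arises at the follow-up time point. In the mixed model of 4.3 it therefore falls into the group-by-time term and cannot be told apart from a treatment effect. It does not shrink as the sample grows. The practice in 4.3 of emphasising unadjusted values would carry it straight into the reported differences. At stake is the credibility of the between-group differences in some secondary outcomes, above all the circumferences.

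**Working it through.** **1. Which outcomes are exposed.** The plan states no figure on this point, so there is none to reproduce. Setting the blinding rule in 4.1 against the methods in 3.6 and 3.7 gives:

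| Outcome | Method | Assessor under 4.1 | Room for observer influence |
|---|---|---|---|
| VAT (primary), other MRI depots | MRI, semiautomatic segmentation, part manual editing | Blinded | Not at issue |
| Glucose, insulin, lipids and other blood markers | Fasting blood sample | Blinded | Not at issue |
| Neck, waist, hip circumference | Manual, ISAK procedure | Not blinded | Greatest |
| Bone mineral density, fat mass, fat-free mass | DXA | Not blinded | Smaller: positioning and scan analysis |
| Body weight | Electronic scale | Not blinded | Minimal |
| Blood pressure | Automatic monitor | Not blinded | Minimal |

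The last column is a judgement from the method of measurement; the documents do not rate it.

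**2. When.** If baseline precedes allocation, as 3.4 suggests, the baseline assessor has nothing to be unblinded to. The risk then sits mainly at week 12.

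**3. Which comparisons.** The aim compares four groups with one another, giving 4 × 3 / 2 = 6 pairwise contrasts. Three are TRE against usual care, where an expected direction is plausible. Three are TRE against TRE, where none is obvious.

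**4. Do the safeguards close the gap?** Training and ISAK reduce random error, but they do not withhold the allocation. Coding and blinded analysis act after the reading has been taken. None of them blinds the week-12 assessor.

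**5. Illustration of size.** The documents give no measurement error, no expected shift and no SD for waist change. The following values are **assumed**: no true effect, an average shift b of 0.5 or 1 cm across a whole arm, and an SD of 12-week waist change of 3 to 5 cm. From 4.2 come n = 21 per arm and alpha = 0.008 (stated there for VAT); alpha = 0.05 is added for comparison. Because 4.3 analyses men and women separately, 21 per arm is the relevant size.

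Formulas: SE = SD × √(2/n). False-positive risk = P(Z > z − b/SE) + P(Z < −z − b/SE), with z = 1.96 for alpha 0.05 and 2.652 for alpha 0.008.

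- SD 3: SE = 3 × √(2/21) = 0.926; for b = 1, b/SE = 1.080. At 0.05: 0.1895 + 0.0012 = 19.1%. At 0.008: 0.0580 + 0.0001 = 5.8%.
- SD 5: SE = 5 × √(2/21) = 1.543; for b = 1, b/SE = 0.648. At 0.05: 0.0948 + 0.0046 = 9.9%. At 0.008: 0.0225 + 0.0005 = 2.3%.

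| Assumed shift, 21 per arm | Alpha 0.05 | Alpha 0.008 |
|---|---|---|
| none | 5% | 0.8% |
| 0.5 cm | 6.2–8.4% | 1.1–1.8% |
| 1 cm | 9.9–19.1% | 2.3–5.8% |

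Ranges run from SD 5 cm to SD 3 cm. With both sexes pooled (21 × 2 = 42 per arm), a 1 cm shift would give 15–33% at 0.05 and 4–13% at 0.008. That shows that a larger sample does not dilute the shift, but it is not the analysis 4.3 describes.

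**The case against.** The strongest case against the point is that the plan protects what matters most. VAT, the other MRI depots and the blood markers are evaluated blind, the open-label components are openly declared, and abdominal fat is also measured by blinded MRI. That stands, and it keeps this a matter of secondary outcomes.

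Several stronger readings are tempting, and the documents do not support them:

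- A reader might infer that blinded and unblinded staff work side by side at the same visit. Section 3.5 gives shared time points only; it says nothing of shared visits or staff.
- A reader might infer that blood samplers are already blinded and could take the tape measurements. The wording of 4.1 fits laboratory analysts and image readers who may never meet a participant, so it does not prove that a face-to-face assessor can easily be kept blind. Staff numbers are not given either.
- A reader might infer that the results are biased toward TRE. The documents support a risk, of unknown size. Usual care receives the same educational programme (3.8), and the TRE-against-TRE contrasts have no obvious expected direction.
- A reader might extend the problem to all body-composition and cardiometabolic outcomes, or to regional DXA measures. The scale and automatic monitor leave little to the operator, and 3.7 names no regional DXA outcome.
- A reader might see intent in the arrangement. The plan specifies it but gives no motive.

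What remains is that the week-12 circumferences are operator-dependent, their assessors know the arm, and no reason or counter-measure is given.

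**Conclusion.** The point holds in this limited form: 4.1 leaves the assessors of all non-MRI, non-blood measures unblinded without explanation, which exposes secondary outcomes at week 12 to observer bias. The exposure is graded: greatest for neck, waist and hip circumference, smaller for DXA, minimal for weight and blood pressure. Only TRE against usual care has a plausible direction.

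The size cannot be derived from the documents. The calculation shows only what a given shift would do, and depends wholly on the assumed shift and SD. A full 1 cm average shift would roughly double to quadruple the nominal 5% error at 21 per arm; half that shift would raise it only modestly. The conclusion that blinding should be improved does not depend on these values, because a group-dependent shift of any size passes through the planned model unchanged. This is a worthwhile, inexpensive improvement and does not threaten the primary result.

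**What to change.** Amend 4.1 as follows:

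- At week 12, circumferences are taken by existing site staff who do not deliver the intervention sessions and have no access to the allocation. The same applies to DXA acquisition, weight and blood pressure where the roster allows.
- Participants are asked not to tell the assessor their arm.
- DXA scans are analysed under code, as for MRI.
- Any unblinding of an assessor is recorded.
- Where existing staff cannot be kept blind for a measure, 4.1 names it as open-label and its between-group difference is interpreted with that limitation. The 24-hour dietary recalls are a likely case, since reported eating times reveal the arm.

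If week-12 measurements have already been taken, coded analysis of the DXA scans and a stated limitation for the circumferences are still possible.

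The cost is a short change to 4.1, restricted access to the allocation, some scheduling effort and occasional disclosure by participants. No new procedure or assessor is required; where a site's existing staff do not suffice, the open-label statement applies instead.

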## **4.2 Sample size**

A recent systematic review and meta-analysis indicate that a VAT reduction of 6.1% is considered a clinically meaningful change even in the absence of weight loss [27]; previous exercise and nutrition intervention trials also showing changes in VAT ranging from 10 to 28% [28, 29]. The sample size calculations for VAT assume the study will be able to detect a mean difference of 10% in each intervention group from baseline to intervention endpoint, relative to the UC group. Therefore, assuming a standard deviation of 7% in VAT [28], the enrolment of 21 participants per arm will provide a statistical power of 90% at an alpha level of 0.008 (controlling for multiple group comparisons) to detect a minimum effect size of 10% in VAT. Considering subgroup analyses by sex and a maximum dropout rate of ~20%, we will recruit ~52 participants for each trial group; the total sample size being of ~208 participants (~104 in each study site).

To ensure a balanced sex distribution and maintain sufficient sample numbers despite projected dropouts, several strategies will be implemented:

- Recruitment process: We will employ a specific recruitment process that aims to enroll an equal number of men and women. For every woman recruited, we will request them to invite one man to participate in the study. This approach has proven successful in our previous intervention studies and has helped maintaining a balanced sex distribution [30-32].
- Sample size calculations: Our sample size calculations have taken into account subgroup analyses by sex. We have conservatively estimated a maximum dropout rate of approximately 20%. By considering this dropout rate, we have ensured that our study is adequately powered to detect the specified effect size even if there are differential dropout rates between men and women. For example, if men have a dropout rate of 5% and women have a dropout rate of

15%, our study will still have sufficient power to analyze the data separately in men and women.

- Expected dropout rate: While we have conservatively estimated the maximum dropout rate, we anticipate that the actual dropout rate will be relatively lower and similar between both sexes. This expectation is based on our previous studies and the measures we have in place to promote participant engagement and adherence [30-32].

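### Section 4.3 names no multiplicity procedure; testing the six VAT contrasts at section 4.2's fixed 0.008 would give up modest power that a step-down test returns within the same 5% family-wise ceiling

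*Combined protocol and SAP*

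**What the plan says.** Section 2 sets out to study three TRE schedules "compared to each other and to a usual-care (UC) intervention". With four arms that makes six pairwise contrasts, although the plan never writes the number six.

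Section 4.2 states that 21 participants per arm "will provide a statistical power of 90% at an alpha level of 0.008", and explains the level as "an alpha level of 0.008 (controlling for multiple group comparisons" in the same sentence. The effect sized for is to "detect a mean difference of 10% in each intervention group from baseline to intervention endpoint, relative to the UC group", "assuming a standard deviation of 7% in VAT". The same paragraph also reports that "a VAT reduction of 6.1% is considered a clinically meaningful change even in the absence of weight loss".

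Section 4.3 describes a mixed model fitted by restricted maximum likelihood and says that men and women are analysed separately. It gives no significance threshold, no list of contrasts and no multiplicity procedure. Neither section names Bonferroni.

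**The concern.** Because 4.3 is silent, 0.008 is the only level an analyst could take from the plan. Applied to each contrast, it is single-step Bonferroni for six pairs, rounded down. That rule ignores two features of the problem. The six contrasts share arms, so their test statistics are correlated. They are also logically linked: once one pair of means differs, at most three of the six equalities can still be true.

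Holm and Shaffer, applied to the same p-values, reject everything that 0.05/6 rejects and sometimes more, with family-wise error still at or below 5%. At stake is some avoidable loss of power for the TRE-versus-UC contrasts within each sex, at effects smaller than the planned 10%.

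**Working it through.** **Inputs.** From 4.2: alpha 0.008, SD 7%, planned difference 10%, clinically meaningful reduction 6.1%, 21 per arm. From 4.1: allocation 1:1:1:1. Assumed: two-sided tests, independent normal arms, and one variance pooled over four arms, so df = 4(n − 1) = 80 at n = 21.

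**The level.** Pairs = 4 × 3 / 2 = 6, and 0.05/6 = 0.00833, so 0.008 is 0.05/6 rounded down.

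**The plan's own figure.** The noncentrality is λ = δ / (SD × √(2/n)). For δ = 10 and n = 21, λ = 10 / (7 × 0.3086) = 4.63. With critical t = 2.720 (0.008 two-sided, 80 df) power is 97.0%, not 90%. On these inputs 90% needs 16 to 18 per arm, depending on the approximation. The stated 21 therefore does not reproduce, which is a separate matter. I keep n = 21 because it is the plan's implied unit within one sex: 2 × 21 = 42, and 42/0.8 = 52.5, close to the ~52 recruited per arm.

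**Rules compared.**
- Fixed: p ≤ 0.008.
- Tukey: |t| ≥ q/√2 = 2.624 on 80 df.
- Holm: ordered p-values against 0.05/6, /5, /4, /3, /2, /1.
- Shaffer: ordered p-values against 0.05/6, /3, /3, /3, /2, /1.

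The fixed and Tukey powers per contrast follow from the noncentral t. For δ = 6.1, λ = 6.1 / (7 × 0.3086) = 2.82, giving 54.4% and 58.1%. The other figures come from simulation with 200,000 replicates (standard error near 50% power: √(0.5 × 0.5 / 200,000) = 0.11 points).

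**One sex, n = 21, all three TRE arms 6.1% better than UC.**

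| Rule | Power per TRE–UC contrast | Gain | Power for all three | Family-wise error, complete null |
|---|---|---|---|---|
| Fixed 0.008 | 54.4% | – | 29.8% | 3.9% |
| Tukey | 58.1% | +3.7 | 33.5% | 5.0% |
| Holm | 57.9% | +3.5 | 36.1% | 4.1% |
| Shaffer | 61.7% | +7.3 | 40.7% | 4.1% |

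Using 0.05/6 unrounded gives 54.9%, so about half a point of each gain is only the rounding to 0.008. Fixed 0.008 reaches 62.1% at n = 24, so Shaffer's gain is worth about three completers per arm per sex.

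**Other settings, gain per TRE–UC contrast over fixed 0.008 (differences taken before rounding).**

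| Setting | Fixed | Tukey | Holm | Shaffer |
|---|---|---|---|---|
| n = 21, all three at 10% | 97.0% | +0.6 | +0.9 | +1.4 |
| n = 42 (sexes combined), all three at 6.1% | 90.3% | +1.4 | +2.0 | about +3.5 |
| n = 21, effects 6.1/3/3%, the 6.1% arm | about 54% | +3.7 | +1.2 | +2.4 |

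**What the step-down spends.** When only UC differs, at n = 21 and 6.1%, the chance of any false TRE-versus-TRE claim is about 2.2% at fixed 0.008, 3.2% with Holm and 4.3% with Shaffer.

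**The case against.** The strongest reply is that the plan does not state the criticised rule. The 0.008 appears only in the sample-size paragraph, and sizing at a conservative level does not prevent Holm or Tukey at analysis. That stands. A reader might infer that the plan commits to single-step Bonferroni testing; it does not. The point is conditional: 4.3 names no rule, and 0.008 is the only level it could fall back on.

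Second, a reader might infer that any better procedure returns about 7 points. Only Shaffer does, within one sex and at 6.1%; Holm and Tukey return about half that. The 6.1% is cited as a meaningful VAT reduction and not as a difference from UC, whose participants also receive the educational programme (3.8). At the planned 10% the gain is negligible. With unequal effects of 6.1/3/3%, Tukey beats both step-down tests for the strongest arm, so no procedure is best everywhere. All of this stands and limits the size of the point.

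Third, the fixed level does buy something, namely fewer false TRE-versus-TRE claims. That is true, but the plan's implied ceiling is 5% and the step-down tests stay under it.

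Fourth, showing Tukey intervals beside Shaffer p-values can confuse. In the main setting, 14.6% of simulated single-sex trials have at least one contrast that is Shaffer-significant with a Tukey interval including zero; the reverse occurs in 2.6%. Tukey is also exact only for balanced, equal-variance, independent arms, which a mixed model with dropout will not quite be. This stands, and the fix has to say which result decides.

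**Conclusion.** The point holds as an optional efficiency gain. Single-step testing at 0.008 is valid but conservative, and Holm or Shaffer recovers power at the same family-wise 5%. Within one sex at 6.1% and equal TRE effects, the step-down gain per TRE-versus-UC contrast is about 3.5 points (Holm) to 7.3 points (Shaffer). Elsewhere it is roughly 1 to 3.5 points.

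These figures rest on SD 7%, 21 or 42 completers per arm, two-sided tests, and a simple four-arm normal comparison in place of the planned mixed model. They concern TRE versus UC. No power gain was worked out for early versus late TRE, so none is claimed. The documents do not support reading this as a breach of error control, a bias, or an underpowered design at the planned 10% effect.

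**What to change.** In 4.3, before unblinding, state that:
- the six pairwise VAT contrasts in each family are tested with one named step-down procedure (Holm, or Shaffer for more power) at a family-wise 5%;
- results are reported as adjusted p-values;
- the step-down p-values decide significance, and any simultaneous intervals shown are descriptive.

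Keep 0.008 in 4.2, labelled as the conservative planning level. What counts as a family, for example each sex, is for the sponsor to define; this change works within whichever definition is chosen.

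The cost is a few sentences and standard software, with no new data or participants. There are two downsides. Step-down tests have no exactly matching intervals, and more of the permitted 5% is spent on possible false TRE-versus-TRE claims.
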